### Standard care group

Patients randomised to the standard of care (control) group will receive their standard clinical care and will be provided with verbal activity advice as per UK government recommendations. Advice on activity will be given after randomisation, and patients will be advised to visit the government physical activity guidelines website.^23^

### Intervention group

The intervention is a physical activity and behavioural change support programme, plus standard care. The physical activity intervention will provide support for 12 weeks; weeks 1–8 will consist of weekly (where possible) direct contact in groups of 4–7 patients and additional individual telephone health coaching once weekly (where possible), then in weeks 9–12, telephone health coaching only will be provided. The intervention will be staged adapted, and participants will be encouraged to increase physical activity within their capabilities. Participants will be provided with personal activity self-monitoring devices, which are wrist-worn accelerometers (Fitbit Model FB405BKL), providing individual feedback on daily physical activity. The supervised activity sessions will incorporate CBS (eg, goal setting, finding social support and understanding the costs/benefits of exercise etc) to promote long-term participation in physical activity. The intervention includes education, monitoring and assessment of progress and teaches skills to improve self-efficacy.

Individual specific, measurable, achievable, realistic and timed (SMART) goals^24^ will be set by the participants with guidance from the intervention facilitator and will focus on increasing activity levels. The behavioural goal is for participants to achieve at least 30 min of moderate intensity activity, 5 days per week, ideally in bouts of 10 min, as per UK government recommendations, although any increase in physical activity or reduction in sedentary time will be viewed positively. The Fitbit activity self-monitor is supported with online web interfaces that facilitate effective components of physical activity interventions (https://www.fitbit.com/login).^25^

A detailed facilitator intervention manual has been developed to support the supervised sessions and telephone coaching. In brief, the physical activity intervention is designed to be pragmatic and accessible, taking into account exercise preferences and giving choices. During the direct contact sessions, participants will be asked to complete short bouts (eg, 5×3 min, with 2 min rest intervals) of low to moderate intensity aerobic exercise (eg, stepping ergometer, cycle ergometer, treadmill walking, rowing ergometer, arm cranking) at 50%–69% of predicted maximum heart rate (220—age) or 12–14 on the Borg Ratings of Perceived Exertion Scale.^26^ Intensity will be monitored continuously during exercise training sessions. As the intervention progresses, participants will be encouraged to participate in longer periods of aerobic exercise (eg, 5×4 min) or to take shorter rests between bouts.

Where appropriate, participants will also be introduced to exercises for strength and control, which will typically involve two to six different resistance exercises (eg, wall press ups, arm curls, leg abduction, wall squats and/or regular squats, knee extensions, calf raises, sit-to-stand) each session. Body resistance, light weights and Therabands will be used to provide resistance and one to three sets of 5 to 20 repetitions will be performed, depending on level of disability and strength, as well as stage of the programme (exercises will be progressed according to individual capabilities and strength gains). Static stretching exercises for large skeletal muscle groups will be included in the sessions.

Participants will be encouraged to replicate the sessions at home supported by the telephone health coaching.

Using activity data collected from the Fitbit device from the preceding week, the intervention facilitator will assist participants to establish SMART goals.^24^ Data collected will be shared with the therapist, via either the internet dashboard or paper diary. Review of daily and weekly physical activity will be undertaken to identify bouts of moderate/vigorous physical activity and to negotiate change plans to increase bouts of moderate/vigorous physical activity.

During the telephone discussion, participants will be encouraged to use their activity profiles generated from their Fitbit device, with data collected and stored using the online dashboard or paper diaries, to promote self-determination and self-regulation to achieve personal goals and maintain activity. The therapist will review fatigue, the impact of physical activity on fatigue and the management of fatigue with the participant. The therapist will review activity plans and understanding, provide physical activity education and help the patient to generate activity maintenance plans and set new goals.

### Study procedures

The study outcomes, measurement methods and assessments are summarised in table 1. Data are collected at baseline, and then at 12, 24 and 52 weeks, from the first exercise session for those in the intervention group and from randomisation for those in the standard care group. Data on recruitment, number of activity sessions and telephone coaching sessions completed and drop outs will also be recorded.

**Table 1 T1:** Visit overview

Visit	Prebaseline	Baseline	Baseline (+4 weeks)	Weeks 1–8	Weeks 9–12	Week 12*	Week 24*	†Week 52*
Identification of eligible patients	x							
Eligibility check	x	x						
Valid informed consent		x						
Relevant medical history taken		x						
Randomisation (without patient present)			x					
Activity advice telephone call (control arm only)‡				x				
Exercise visits (intervention arm only)				x				
Weekly telephone coaching contacts (intervention arm only)				x	x			
Follow-up clinic visits*§						x	x	
Final assessment (postal questionnaires)*§								x
Quality of life questionnaires		x				x	x	x
Focus groups or interviews (postintervention)					x	x	x	

*The timing of the follow-up visits for intervention group are taken from intervention start date, not randomisation date; for the control group, the timing is taken from randomisation date.

†52 weeks follow-up assessment can be completed—2 weeks before due date and up to 8 weeks after the due date.

‡Control group have one telephone call in week 1 (postrandomisation) to receive standard activity advice only.

§12-week and 24-week follow-up assessments can be completed up to—2 weeks before due date and up to 3 weeks after the due date.

At the baseline, 12-week and 24-week assessments blood pressure, height (baseline only), weight and waist circumference will be measured, disease type, medical and drug history (baseline only), use of immunosuppressive therapy and assessment of damage associated with AAV, using the vasculitis damage index^27^ (baseline only) will be taken. Laboratory investigations, including full blood count and kidney function are measured at baseline. At each assessment visit, disease activity will be assessed using the BVASv3. Clinical outcomes and safety of the intervention, including muscle or bone injury, disease relapse and cardiovascular adverse clinical events will be collected at 12 and 24 weeks as self-reported by the participant. All serious adverse events will also be recorded. Participants will complete a suite of validated health-related quality of life and fatigue questionnaires, which include short form-36 (SF-36),^28^ ANCA Vasculitis questionnaire (AAV-PRO), EQ-5D,^29^ MFI-20,^30^ Pittsburgh Sleep Index,^31^ Bristol Rheumatoid Arthritis Fatigue-Multidimensional questionnaire,^32^ Hospital Anxiety and Depression score,^33^ Brief Coping Orientation to Problems Experienced (Brief COPE) questionnaire^34^ and the International Physical Activity Questionnaire long version at baseline and at 12, 24 and 52 weeks (at 52 weeks, the participants will be contacted by post and asked to complete the same questionnaires as completed at previous assessments and to return these by post or at next clinic visit). All participants will be asked to wear an accelerometer (GENEActive GATV01, Activinsights, Kimbolton, UK) for 7 days at baseline and at 12 and 24 weeks to provide an objective measure of their activity.

In order to undertake an analysis of all the direct resources and costs required to deliver the intervention, a detailed collection of health economic data will be embedded within the trial.

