## Methods

### Overview of study design

This is a single centre, open-label randomised controlled feasibility study with a nested qualitative component. Feasibility will be determined by assessing recruitment, adherence to the intervention and retention rates. Acceptability and patient experience will be assessed through patient-reported outcome (PRO) questionnaires, and an optional nested qualitative study consisting of either focus groups or semistructured telephone interviews if insufficient numbers can be recruited to form focus groups.

Fifty participants will be randomised (via a computer-generated programme) in a 1:1 ratio to the intervention or standard care for this population (figure 1 study flow). The randomisation will be minimised by age (<65 vs ≥65 years). Participants randomised to the intervention arm will complete eight supervised (one per week) and 12 telephone coaching sessions over 12 weeks. Outcomes will be assessed at baseline, 12, 24 and 52 weeks from the first exercise session for those in the intervention group and from randomisation for those in the standard care group.

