### Participants and recruitment

Patients will be recruited to the study via the dedicated vasculitis service at University Hospitals Birmingham NHS Foundation Trust (UHB NHSFT) or via response to study adverts placed in the Vasculitis UK newsletter or other hospital clinics. Confirmation of eligibility for the study will be with the patient’s own clinician. Patients are eligible if they are 18 years of age or older, have a diagnosis of AAV as classified by the European Medicines Agency Algorithm,^21^ have been in remission for at least 6 months on the day of consent (defined by Birmingham Vasculitis Activity Score Version 3 (BVASv3)^22^=0 on day of consent and prednisolone dose <7.5 mg for 6 months) and have significant fatigue levels (multidimensional fatigue inventory (MFI)-20 general fatigue score ≥14). Exclusion criteria include inability to provide informed consent, inability or unwillingness to undertake physical activity, comorbidities considered by their own clinician to contraindicate an increase in physical activity and an inability to understand and complete questionnaires.

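### Relapse, a secondary safety outcome, is recorded from participant self-report in an open-label trial, although the BVASv3 that defines remission at entry is scored at the same visits

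*Protocol article*

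**What the plan says.** Study procedures in the protocol article names relapse among the safety outcomes: "Clinical outcomes and safety of the intervention, including muscle or bone injury, disease relapse". It then gives the source: "disease relapse and cardiovascular adverse clinical events will be collected at 12 and 24 weeks as self-reported by the participant". The sentence just before reads: "At each assessment visit, disease activity will be assessed using the BVASv3". Table 1 places clinic follow-up at weeks 12 and 24 and makes week 52 a postal assessment, so BVASv3 is in hand at the two visits where relapse is asked about.

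Participants and recruitment defines the starting state clinically. Patients must "have been in remission for at least 6 months on the day of consent", which means BVASv3 = 0 on that day together with a prednisolone limit. It adds: "Confirmation of eligibility for the study will be with the patient’s own clinician". The same section requires that patients "have significant fatigue levels (multidimensional fatigue inventory (MFI)-20 general fatigue score ≥14").

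Overview of study design states: "This is a single centre, open-label randomised controlled feasibility study". Study outcomes and data analysis plans descriptive summaries of all clinical outcomes and, where appropriate, effect estimates such as relative risks with 95% confidence intervals. Study procedures also says that all serious adverse events are recorded.

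**The concern.** The trial uses two standards for one disease state. Remission is established by a scored instrument and a treatment criterion; its loss is whatever the participant says at week 12 or 24. Nothing in the article says what happens when the two records disagree, for example a self-reported relapse with BVASv3 = 0, or a raised score with no relapse reported.

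Error is possible in both directions. Every participant enters with significant fatigue, and a worse spell may be reported as a flare. A mild relapse may equally go unrecognised, or be put down to exercise. The error may also differ by arm, because participants know their allocation and are prompted unequally. The intervention arm is scheduled for 8 supervised sessions and 12 calls, with fatigue and the effect of activity on it reviewed during the calls. The control arm has one advice call.

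What is at stake is a small safety table. Non-serious relapses would be tabulated by arm from unverified reports. The study also has an objective of testing outcome measurement for the definitive trial, so a weak relapse measure could be carried forward.

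**Working it through.** The plan gives no relapse rate and no formal sample size calculation, so there is no figure of its own to reproduce.

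**Inputs from the article.** 50 participants randomised 1:1, so about 50 / 2 = 25 per arm. Relapse by self-report at weeks 12 and 24. BVASv3 at the same visits. Scheduled contacts in the first 12 weeks: 8 + 12 = 20 in the intervention arm against 1 call in the control arm.

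**Step 1: weight of one misclassified participant.** 1/25 = 4 percentage points in that arm.

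**Step 2: two false reports in one arm (assumed).** Suppose the true counts are 2/25 and 2/25, or 8% in each arm. Two false reports in one arm give 4/25 = 16% against 2/25 = 8%, a relative risk of 16/8 = 2.0.

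**Step 3: bias in a single rate (assumed values).** Let p be the true relapse risk, and Se and Sp the sensitivity and specificity of self-report. The apparent rate is p × Se + (1 − p) × (1 − Sp). With p = 0.10:
- Se 0.5, Sp 1.0: 0.10 × 0.5 + 0.90 × 0 = 5.0%, too low.
- Se 0.9, Sp 0.85: 0.10 × 0.9 + 0.90 × 0.15 = 22.5%, too high.

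Between the same two settings, the apparent rate runs from 2.5% to 18.8% for p = 0.05, and from 7.5% to 26.3% for p = 0.15.

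**Step 4: reporting that differs by arm (assumed values).** Keep the true risk at 10% in both arms.
- One arm, Se 0.9 and Sp 0.85: 22.5%.
- Other arm, Se 0.7 and Sp 0.95: 0.10 × 0.7 + 0.90 × 0.05 = 11.5%.
- Ratio 22.5 / 11.5 = 1.96, or 11.5 / 22.5 = 0.51 if the arms are swapped.

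**Step 5: comparison with sampling error.**
- Exact (Clopper-Pearson) 95% interval for 2/25: 1.0% to 26.0%. For 5/25: 6.8% to 40.7%.
- Relative risk for 4/25 against 2/25: standard error of the log is √(1/4 − 1/25 + 1/2 − 1/25) = √0.67 = 0.82, so the 95% interval is about 0.4 to 10.
- Relative risk for 2/25 against 2/25: standard error √(1/2 − 1/25 + 1/2 − 1/25) = √0.92 = 0.96, so the interval is about 0.15 to 6.6.

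These intervals are at least as wide as the shifts in Steps 2 to 4. Steps 2 to 4 show what misreporting could do. They do not estimate what it will do.

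**The case against.** The other side has a good deal of substance. The article condenses a fuller protocol, and a relapse definition, form instructions and source checks often sit there or in the analysis plan. Self-report also has a use, since two visit scores can miss a relapse that arises and settles between visits. BVASv3 is collected in both arms, and serious relapses should appear as serious adverse events. The trial is not powered to compare arms, so perfect adjudication would not settle a relapse comparison. The documents mention no blinded assessor, so BVASv3 may be scored with knowledge of allocation too. Weekly coaching is offered where possible and ends at week 12, so unequal prompting does not extend through weeks 12 to 24.

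These points lower the importance without removing the problem. The article is not silent: it states self-report as the source in the sentence after the one on BVASv3. Non-serious relapse would still rest on unverified reports, and a confidence interval neither shows nor corrects bias.

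Three stronger readings are tempting and should not be made.
- **That relapse is a main safety question of this study.** Under Aims and objectives, the safety objective names injury and deterioration in fatigue, not relapse.
- **That follow-up treatment data are certainly available as a check.** Study procedures lists "use of immunosuppressive therapy" among the items for baseline and weeks 12 and 24, but a baseline-only note later in the same sentence leaves its timing unclear. The BVASv3 statement is clear and is enough.
- **That self-reported relapse decides the stop-go result.** The rule leaves out patients who drop out or cannot adhere because of disease activity, without saying how that is judged. If self-report were used, leaving out 2 non-adherent patients of 25 would move adherence from 18/25 = 72% (amber) to 18/23 = 78% (green). The article does not say that it will be used, so the point does not rest on this.

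**Conclusion.** The concern holds as a minor point. The article fixes participant self-report as the source of a named safety outcome in an open-label trial, while the instrument that defined remission at entry is scored at the same visits and is not linked to it. The size is 4 percentage points in an arm's rate per misclassified participant, assuming about 25 per arm.

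A reader might infer that the relapse comparison will be biased, or biased towards harm from exercise. The documents do not support that: they give no relapse rate, no reporting accuracy and no direction, and the relative risks of 2.0, 1.96 and 0.51 depend on assumed inputs. What is established is that the recorded rate can be wrong in either direction, possibly differently by arm, with no stated check against a measure already collected.

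**What to change.** State one rule for the reported relapse outcome and apply it identically in both arms:
- Base it on the BVASv3 already scored at weeks 12 and 24.
- Treat a participant's report as a prompt to look for a relapse between visits, and count it once confirmed from the clinic record or by the patient's own clinician. Confirmation may draw on a treatment change for active vasculitis where one is recorded.
- Tabulate unconfirmed self-reports separately by arm.

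It would also help to clarify whether immunosuppressant use is collected at follow-up or only at baseline.

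This changes how an outcome is measured, not how patients are managed, and BVASv3 needs no new collection. The cost is protocol wording and a few record checks, some at other hospitals for participants recruited outside the vasculitis service. One limit remains: BVASv3 scoring and clinician confirmation may themselves be made with knowledge of allocation, so the rule reduces the problem without removing it.

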### Study outcomes and data analysis

The primary outcome of this feasibility trial is to determine if a full RCT comparing physical activity with behaviour change support versus standard care in patients with AAV is feasible. This decision will be made using a composite assessment of both quantitative and qualitative data based on a traffic light system using predefined stop-go criteria. The three criteria contributing to the traffic light system include^1^ recruitment rates, defined as the proportion of eligible patients recruited into the study^2^; successful adherence to the intervention, defined as attendance at a minimum of 4 of the 8 visits for the face to face support, and acceptance of a minimum of 3 of the 4 telephone support calls in weeks 9–12 and^3^ study drop-out, defined as complete withdrawal from the study, with no further data collected from the participant. The traffic light system comprises (1) green light: recruitment rate >50%; adherence rate >75% and drop-out rate <15% excluding those patients who drop-out or are unable to achieve adherence due to disease activity. If all three criteria are met, we will proceed to a full trial with the protocol unchanged (unless there is a clear message from the qualitative work that would improve the protocol). (2) Amber light: recruitment rate 30%–50%, adherence rate 50%–75% or drop-out rate 15%–30% excluding those patients who drop-out or are unable to achieve adherence due to disease activity. If one or more of our amber light criteria are met, we will adapt the protocol in light of the result of the feedback from the qualitative work and our experience to improve whichever criteria are not at the ‘green-light’ level before proceeding to full trial if possible. We will assess whether adaption of the protocol will require a further feasibility study or pilot study before progressing. (3) Red light: recruitment rate <30%, adherence rate <50% or drop-out rate >30% excluding those patients who drop-out or are unable to achieve adherence for disease activity. If one or more of these criteria are met we would consider the current protocol not feasible and not progress to a full RCT.

The primary analysis to assess the stop-go criteria will be undertaken once all participants have completed the 24-week assessment, and corresponding outcome data has been entered onto the study database and validated as being ready for analysis. Feasibility outcomes including the three components of the stop-go criteria will be analysed by pooling the two randomised groups and presenting overall estimates with 95% CI. Reasons for non-entry into the trial will be assessed, particularly in relation to the patient eligibility criteria and reasons for patient refusal. Data on patients who stop the intervention and/or who do not complete the trial (such as withdrawals and those lost to follow-up) will be collected throughout the trial to allow assessment of patient adherence and retention rates. Reasons for non-adherence and non-completion will be analysed descriptively.

All clinical and patient-reported outcomes will primarily take the form of simple descriptive statistics (eg, proportions and percentages, means and SD) and where appropriate, point estimates of effects sizes (eg, mean differences and relative risks) and associated 95% CI. Data return rates at each time point will be assessed along with data completeness of the various outcomes measures. This will inform the use of appropriate questionnaires for the primary outcome in a future study. The data will be analysed using the intention to treat principle, where patients are analysed in the treatment group to which they were randomised regardless of adherence to intervention or compliance with the protocol.

Detailed data collection of the resources required to deliver the intervention will allow a cost analysis to be undertaken to calculate the cost of implementing the intervention in a full RCT. The mean cost of the intervention per patient will be estimated both as per usage in the study and also the full cost assuming full compliance. Data collected directly from the trial will determine the resources required for delivering the supervised exercise and telephone health coaching. Resources will include staff costs, any equipment/consumables needed, printed material, telephone call costs, staff training costs and infrastructure (eg, room space). Information will be collected on number of patient contacts, length of time for face to face and telephone contacts and group size for the supervised exercise sessions. Standard unit costs for healthcare will be applied, with local costs sought from participating healthcare providers. Sensitivity analysis will estimate costs with changes to costing assumptions, for example, staff grade, group size.

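### The stop-go drop-out criterion counts only complete withdrawal, so the retention light can be green while more than 30% of 24-week outcomes are missing

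*Protocol article*

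**What the plan says.** All of this is in the protocol article, mostly under Study outcomes and data analysis.

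- The primary outcome is a traffic-light decision on whether a full trial is feasible, built on recruitment, adherence and drop-out. The third is "study drop-out, defined as complete withdrawal from the study, with no further data collected from the participant".
- Green is "green light: recruitment rate >50%; adherence rate >75% and drop-out rate <15% excluding those patients who drop-out or are unable to achieve adherence due to"; the reason excluded is active vasculitis. For the middle band the text gives "Amber light: recruitment rate 30%–50%, adherence rate 50%–75% or drop-out rate 15%–30"%, and for the lowest "Red light: recruitment rate <30%, adherence rate <50% or drop-out rate >30"%.
- On an all-green result: "If all three criteria are met, we will proceed to a full trial with the protocol unchanged". The one stated exception is a clear message from the qualitative work.
- The stop-go analysis "will be undertaken once all participants have completed the 24-week assessment".
- Outside the rule, the plan collects data on patients who "do not complete the trial (such as withdrawals and those lost to follow-up") and analyses the reasons descriptively. It also assesses return rates and completeness at each time point, to guide the choice of questionnaire for a future trial. None of these has a cut-off.
- Overview of study design: "Fifty participants will be randomised (via a computer-generated programme) in a 1:1 ratio".
- Aims and objectives lists the assessment of retention among the study's objectives.

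**The concern.** Retention belongs in a progression rule to show whether a definitive trial could observe its outcome in the people it randomises. The criterion as worded measures something narrower: whether people have left the study entirely. Someone who remains enrolled but misses the 24-week visit, or attends and returns no fatigue questionnaire, is not a drop-out. None of the three criteria requires a 24-week outcome, although the decision is timed to that assessment.

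The adherence criterion closes part of the gap, but only in the intervention arm and only up to week 12, because it is built from supervised visits and from telephone calls in weeks 9–12. Controls receive one advice call in week 1, so drop-out is the only criterion that follows them after randomisation.

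At stake is the primary outcome itself. The rule, followed exactly, could send the design forward unchanged when a third or more of its 24-week outcomes were not obtained.

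**Working it through.** The protocol gives no figure for expected drop-out or missing data, and no formal sample size calculation, so there is nothing to reproduce. The check applies the plan's own cut-offs to its own sample size.

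**Inputs from the protocol article.** N = 50, allocated 1:1 (about 25 per arm); drop-out green <15%, amber 15%–30%, red >30%; adherence green >75%.

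**Assumed input.** The number of participants who have not withdrawn but have no 24-week outcome. The protocol gives none, so 0 to 20 is shown.

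**Step 1: cut-offs as counts.** 0.15 × 50 = 7.5 and 0.30 × 50 = 15. Green is 0–7 drop-outs, amber 8–15, red 16 or more. At the green limit, 7/50 = 14% (exact 95% CI 5.8% to 26.7%).

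**Step 2: score as written against outcomes missing.** Let w be complete withdrawals, assumed here to have no 24-week outcome, and m the others without one. The rule scores w/50. The share of outcomes missing is (w + m)/50. Each cell in the last four columns gives that share and the colour the same cut-offs would assign to it.

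| w | Score as written | m = 5 | m = 10 | m = 15 | m = 20 |
|---|---|---|---|---|---|
| 0 | 0%, green | 10%, green | 20%, amber | 30%, amber | 40%, red |
| 3 | 6%, green | 16%, amber | 26%, amber | 36%, red | 46%, red |
| 6 | 12%, green | 22%, amber | 32%, red | 42%, red | 52%, red |
| 7 | 14%, green | 24%, amber | 34%, red | 44%, red | 54%, red |

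The score as written does not move with m. Missing outcomes pass the red line once w + m reaches 16, that is at m = 16 − w: 16 others when nobody withdraws, 10 when six do, 9 when seven do. For 16/50 = 32% the exact 95% CI is 19.5% to 46.7%.

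**Step 3: would adherence catch it?** 0.75 × 25 = 18.75, so green needs 19 of 25 adherent (76%) and 6 may fail. Take w = 6 and m = 10. Suppose all six withdrawals are in the intervention arm and all fail adherence, and the ten others are controls. Adherence is 19/25 = 76%, green. Drop-out is 6/50 = 12%, green. Yet 10/25 = 40% of control outcomes and 16/50 = 32% overall are missing. Only recruitment above 50% is then needed for all green. Loss in the intervention arm after week 12 would also leave adherence unchanged.

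**Step 4: the disease-activity exclusion.** Suppose 5 withdrawals are due to disease activity. If the denominator stays at 50, 7 more may withdraw: 12/50 = 24% in total, still green. If it falls to 45, 6 more may (6/45 = 13.3%): 11/50 = 22% in total. The article does not say which denominator applies.

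**The case against.** Several objections have force.

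- **Silent loss is ambiguous.** The definition does not require a formal act of withdrawal, and a person who vanishes for good does yield no further data. The text on non-completion names withdrawals and losses to follow-up side by side as examples, and does not say that losses fall outside drop-out. This stands, so silent loss is only arguably excluded. It does not rescue the criterion: on the wider reading, someone still in contact who gives no 24-week outcome is still not counted.
- **The missing data will be visible.** Return rates, completeness and non-completion are all to be reported. True, but they have no threshold, and the only stated exception to an all-green result is qualitative.
- **Adherence catches early disengagement.** It does so in part, in the intervention arm. Control-arm loss and loss after week 12 remain.
- **The future primary outcome is open.** The protocol does not name MFI-20 or 24 weeks for the definitive trial, so a remedy should not treat either as settled. This stands.
- **The cut-offs were set for complete withdrawal.** Applying them to a broader quantity makes the test stricter. True; it should be done knowingly.

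A reader might also infer three stronger claims that the document does not support. First, that the criterion cannot be evaluated at 24 weeks because the 52-week questionnaire is still due: if a withdrawal is what counts, its status is known at that point. Second, that withdrawal is always the smaller number: it is usually no larger than the number of missing outcomes, but the two can be equal, and someone may give 24-week data and withdraw before the analysis. Third, that the definitive trial would be undersized: nothing says the drop-out figure becomes its attrition allowance, and the reported return rates would be available to its designers.

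**Conclusion.** The point holds as a defect in how a component of the primary outcome is defined. With 50 randomised, up to 7 complete withdrawals score green irrespective of how many other participants lack 24-week data. With six withdrawals, ten further missing outcomes are enough to put the true shortfall at 32%, past the plan's own red line, and this pattern is compatible with green on adherence too.

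The size rests on an assumed number of participants who remain enrolled without a 24-week outcome; the protocol offers no estimate, and if that number is small the two measures nearly agree. That the rule disregards such participants does not depend on the assumption. The conclusion is limited to the go/no-go decision. The wording should be settled before the stop-go analysis.

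**What to change.** For the stop-go rule, count as not retained any randomised participant with no fatigue outcome within the 24-week assessment window, whether withdrawn, lost to follow-up or not returned. MFI-20 is a convenient choice because it already defines eligibility and is collected at 24 weeks; the text should say that using it here does not fix the definitive trial's primary outcome. Keep the 15% and 30% cut-offs. State explicitly whether participants lost because of disease activity leave the numerator only or the denominator as well. Report complete withdrawal separately, preferably by arm.

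The cost is a change of definition: the data are already being collected. The retention figure becomes less favourable and the test stricter, since green would then need at least 43 of 50 participants with an outcome, before any disease-activity exclusion.
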